### Aims and hypotheses

Our primary objective is to investigate whether the addition of a CCT program to ongoing LLD treatment (i.e., pharmacotherapy and/or psychotherapy) will help reduce depressive symptoms more so than a placebo training. Outcomes will be assessed 1 month post-training (T1) and during follow-up assessments at three (T2), six (T3) and 12 months (T4). We expect symptom reductions in the participants having received CCT to be greater than in the participants having completed the placebo training at all timepoints. Our second aim is to see whether CCT also exerts effects on other clinical measures including rumination (both trait and state), cognitive emotion regulation, working memory functioning (near and far transfer), inhibition, and quality of life. We expect that participants in the intervention group will show lower rumination, more adaptive cognitive emotion regulation, more improved working memory functioning, inhibition, and quality of life than the participants in the placebo group. Our third aim is to identify working mechanisms of CCT. We will examine whether improved working memory and reduced rumination mediate the effects of CCT on depressive symptoms, hypothesizing that improvements in depressive symptoms will follow improvement of working memory and reduction of rumination in the intervention group. Fourthly, we aim to study individual differences that could account for differences in the effect of CCT on symptom change, where we expect that baseline cognitive control, depression severity, and age will be moderating factors. Our fifth aim is to determine the cost-effectiveness of our add-on CCT, we will conduct a health-economic evaluation and budget-impact analysis, anticipating that CCT will reduce mental healthcare consumption during the follow-up period more so than placebo training. Finally, for our sixth aim, we will be assessing the acceptability and feasibility of the intervention by conducting qualitative interviews with subsamples of participants having received CCT, therapists involved in mental health care for older persons and other stakeholders to inform the further implementation of CCT as an add-on intervention next to existing treatments for LLD.

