### Procedure

#### Recruitment, baseline assessment and randomization

A depression experience expert (author PO) provided input on the intervention and application procedure before the start of the trial. The recruitment and assessment process is illustrated in a flowchart shown in Fig. 1. Clinicians will provide eligible candidates with basic information about the study on paper and/or through an informative video. Clinicians will only inform patients capable of consenting to participation. Interested candidates are referred to the researchers who will provide further information by phone. Eligible participants will be asked to provide their written and informed consent for participation at their first visit to the treatment site, where they will subsequently complete the baseline assessment (T0) gauging depressive symptoms, cognitive functioning, rumination, cognitive emotion regulation, quality of life, and health-care consumption, and health-related disability (economic evaluation). If inclusion criteria are satisfied, participants are randomly assigned to the intervention (CCT) or the active control condition (placebo training) by computer-generated allocation stratified for depression severity as assessed with the Inventory of Depressive Symptomatology Self Report: mild (IDS-SR < 38), moderate (IDS 39–48) and severe (IDS > 49) [52]. At the end of the baseline assessment, all participants are provided with a digital tablet to enable them to complete the eight training sessions in their own homes. Researchers will explain, demonstrate and practice the use of the tablet and schedule the training sessions together with the participant. During the one-month training period, participants will receive email notifications to remind them of the task, while researchers will regularly contact them by phone to monitor their progress, with the number and timepoint of the telephone contacts being documented for each participant.

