### Statistical analyses

#### Sample size calculation

A previous power calculation based on MDD studies demonstrated that an effect size of η^2^ = 0.11 or larger should be attainable [35]. This is equivalent to a standardized mean difference of Cohen’s d = 0.70 or larger. In the current study protocol, which is powered based on the expected effect on the primary outcome measure, we prefer to make a more conservative assumption regarding the expected effect size and opt for d = 0.45, corresponding to a medium-size effect, which would be relevant from a clinical point of view. Effects of d = 0.45 (if present) will be statistically significant in a baseline adjusted ANCOVA with one baseline (post-training) and four follow-ups (at 3, 6, and 12 months) at α = 0.05 (2-tailed) and a power of (1-ß) = 0.80. Assuming a correlation of *r* = 0.50 between baseline and first follow-up and again *r* = 0.50 between subsequent follow-ups, we need *n* = 33 per condition to attain a well-powered study.

However, we will also take into account that the data of the participants will be ‘clustered’ within treating clinicians, which introduces a design effect of de = 1.56 when the mean cluster size is m = 10, the coefficient of variation is cv = 0.475, and the intraclass correlation icc = 0.05 [21]. Multiplying the sample size (*n* = 33 per condition) × the design effect de = 1.56 indicates that, at baseline, we need *n* = 52 per condition or *n* = 104 for both arms. We will not compensate for loss to follow-up because we will conduct intention-to-treat analyses (i.e., including all participants as randomized) as per the CONSORT statement – either using (generalized) mixed models or multiple imputation of missing observations.

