#### Evaluation of clinical outcomes

All analyses will be conducted in agreement with the intention-to-treat (ITT) principle as per the CONSORT statement [40]. We will repeat the analyses in the per-protocol sample: participants who completed at least six training sessions. We will use two-level generalized mixed models on the longitudinal dataset to analyze the clinical outcomes over all 4 time points with condition, time and the interaction of condition x time as factors and the depended baseline measure as covariate while accounting for the multilevel data structure with participants being ‘nested’ in clinicians and assessments ‘nested’ within participants [27]. We will examine baseline cognitive control, depression severity, and age as possible moderators. We will examine the latter as possible moderating variable, because age was a relevant correlate for the effect of the aPASAT on depressive symptoms [12]. Rumination and working-memory functioning will be evaluated as potential mediators of change in depressive symptoms, for which Hayes’ PROCESS macro (in SPSS) will be used. These evaluations of the clinical outcomes will be carried out in SPSS [30] and Stata [58].

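### As written, the secondary-outcome models leave out baseline IDS-SR, the variable that stratified randomisation; if it predicts those outcomes beyond their own baseline, a little precision is given up

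*Protocol article*

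**What the plan says.** In the protocol article, Recruitment, baseline assessment and randomization, participants are assigned by "computer-generated allocation stratified for depression severity as assessed with the Inventory of Depressive Symptomatology Self Report", in three categories (mild, moderate, severe).

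Evaluation of clinical outcomes then sets out one model form for the clinical outcomes. It is a two-level generalized mixed model with "condition, time and the interaction of condition x time as factors and the depended baseline measure as covariate", and it allows for nesting within clinicians and within participants. The only baseline term it names is thus "the depended baseline measure as covariate". The only other mention of severity in that section is "We will examine baseline cognitive control, depression severity, and age as possible moderators".

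The second aim (Aims and hypotheses) covers "other clinical measures including rumination (both trait and state), cognitive emotion regulation, working memory functioning (near and far transfer), inhibition, and quality of life". In Table 1, RRS, BFT, CERQ, PASAT, RNG and Stroop are measured at baseline and T1 only. EQ-5D-5L is measured at baseline, T2, T3 and T4, and WHODAS at all five timepoints. IDS-SR is measured in everyone at baseline.

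**The concern.** For IDS-SR, its own baseline and the stratification variable are the same measure, so the stated model respects the design. For the eight secondary measures they differ, and the stated model contains no term for severity.

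This can matter in two ways. First, a variable known for every participant that may explain part of the outcome is left in the residual. Second, stratification balances severity between the arms, so severity contributes less to chance differences between them, yet its variation still counts in full in the residual. The model's standard error then overstates the true sampling variation, which makes tests conservative.

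At stake is some precision on the second aim in a trial of 104 people. Six of the eight measures have a single follow-up and so gain nothing from repeated assessment. Naming severity as a possible moderator does not resolve this, because a moderator analysis is separate from the covariate list of the main-effect model.

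**Working it through.** **The plan's own figure.** The Sample size calculation uses "opt for d = 0.45, corresponding to a medium-size effect", with "α = 0.05 (2-tailed) and a power of (1-ß) = 0.80" and correlations of "0.50 between baseline and first follow-up and again" 0.50 between follow-ups.

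- Unadjusted: n = 2(1.960 + 0.842)²/0.45² = 77.5 per arm.
- Repeated-measures ANCOVA factor with m follow-ups and r = 0.50: (1 + (m − 1)r)/m − r². For m = 3 this is 0.4167, so n = 32.3, rounded up to 33, as stated. (The text says four follow-ups but lists three times; m = 4 would give 29.1, so 30.)
- Design effect: 1 + ((0.475² + 1) × 10 − 1) × 0.05 = 1.56. Then 33 × 1.56 = 51.5, so 52 per arm and 104 in total.

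The figure reproduces. It concerns the primary outcome, whose model already contains baseline IDS-SR, so it does not bear on this point. No power or precision figure is given for any secondary outcome.

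**Effect of the omission.** Let rp be the partial correlation of baseline IDS-SR with the secondary outcome, given that outcome's own baseline. Adding IDS-SR multiplies the residual variance by (1 − rp²). The interval without it is therefore wider by the factor 1/√(1 − rp²). At rp = 0.3, for example, 1/√0.91 = 1.048. The documents do not give rp, so a range is shown.

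**Check by simulation.** Each setting used 6,000 trials of 104 participants, three equal strata, permuted blocks of 4, and ANCOVA with one follow-up. The correlation of 0.5 between own baseline and outcome is borrowed from the primary outcome. The correlation of 0.5 between IDS-SR and the own baseline, the block size and the equal strata are assumptions. Clinician clustering was not modelled. As a sanity check, the expected standard error with own baseline only is √(0.75 × 2/52) = 0.170, and the simulated mean was 0.170.

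| rp (assumed) | Excess width from omission (formula) | Simulated width with stratum added, relative to own baseline only | Same, with continuous IDS-SR | Coverage of 95% interval, own baseline only |
|---|---|---|---|---|
| 0 | 0% | 1.001 | 1.002 | 95.1% |
| 0.1 | 0.5% | 0.998 | 0.997 | 95.0% |
| 0.2 | 2.1% | 0.986 | 0.982 | 94.8% |
| 0.3 | 4.8% | 0.967 | 0.956 | 95.6% |
| 0.4 | 9.1% | not run | 0.918* | 96.0%* |
| 0.5 | 15.5% | 0.903 | 0.868 | 96.8% |

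*From a separate run of the same kind: mean standard error 0.1562 against 0.1701, and null rejection of 4.0% without IDS-SR against 5.1% with it.

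The simulation error of a coverage figure is about √(0.05 × 0.95/6000) = 0.28 percentage points. Conservatism is therefore not visible at rp of 0.2 or below, is marginal at 0.3, and is clear at 0.4 and above.

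**In participants.** The equivalent sample size with IDS-SR added is 104/(1 − rp²): 108 at 0.2, 114 at 0.3 and 124 at 0.4. Omission thus costs the equivalent of about 4, 10 and 20 participants.

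**The case against.** The strongest objection is that this is a condensed article whose analysis plan is not shown. The model takes one sentence, the covariate list is not said to be complete, and stratification factors are often dealt with in the analysis plan. A reader might infer that the trial will certainly adjust for nothing else; the article does not establish that. What remains is that the article goes beyond silence: it names the factors and the covariate, and that stated specification leaves the stratification variable out of the secondary models. If an analysis plan already includes it, the remedy is only to align the article's text.

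The second objection is that the loss is conditional. A reader might conclude that precision is definitely lost and intervals definitely too wide. The documents do not support that, because they report no correlation between baseline IDS-SR and any secondary outcome. The measures range from self-report scales to performance tasks, so one value is unlikely to suit all of them. At a partial correlation of 0.1 or less the effect is negligible. This objection stands, and the point is worded to match.

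The third objection is that the check is simpler than the planned analysis. It has one follow-up and no clinician clustering. The single follow-up fits six of the eight measures; EQ-5D-5L and WHODAS have more. This stands as a limit on the figures, not on their direction.

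Finally, adding a covariate is not entirely free. At zero partial correlation the interval is wider by a factor of 1.002. The plan also allows generalized models: BFT, for instance, counts negative intrusions over 12 signals. With a non-linear link, adding IDS-SR can change the effect being estimated as well as its standard error. This stands and is carried into the fix.

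**Conclusion.** The point holds as a minor, conditional matter of efficiency. As stated, the secondary-outcome models omit the variable used to stratify randomisation. If baseline IDS-SR predicts an outcome beyond its own baseline, intervals are wider by about 0.5%, 2%, 5% and 9% at assumed partial correlations of 0.1, 0.2, 0.3 and 0.4, and by nothing at zero. Nothing in the documents says where in that range any measure lies.

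Two stronger readings should be resisted. One is that the secondary results would be biased or falsely significant. The error runs the other way: coverage in the check was at nominal within simulation error, or above it. The other is that the primary analysis or the sample size is compromised. The primary model contains baseline IDS-SR, and the stated 33, 52 and 104 are unaffected.

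**What to change.** In Evaluation of clinical outcomes, add a clause saying that the models for secondary outcomes include baseline IDS-SR, as a continuous score or as the severity stratum, alongside the outcome's own baseline. The continuous score recovered slightly more precision in the check. It also avoids having to place scores of 38 and 49, which the printed category limits leave unassigned.

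For any outcome fitted with a non-linear link, state that the treatment effect is then conditional on baseline IDS-SR.

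The cost is one degree of freedom per model, or two for the three-level stratum. No new data are needed, and the loss is negligible if IDS-SR turns out not to be predictive. The clause should be fixed before unblinding so that the covariate is not chosen after the fact.

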#### Rumination and cognitive emotion regulation

##### RRS

The Ruminative Response Scale (RRS) will be used to assess trait rumination [46] at T0 and T1. The Dutch version contains 22 items and demonstrated good internal consistency.

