##### BFT

The breathing focus task [28], also administered at T0 and T1 only, serves to measure state rumination. Participants are asked to close their eyes and focus on their breathing for 5 minutes. Throughout, they will hear 12 random sound signals and after each signal they are asked to report whether they are focusing on their breathing. If they are not, they are to rate the nature of the intrusion as positive, negative, or neutral, and describe the thought briefly (e.g., negative - my depression). The number of negative intrusions reflects the severity of rumination.

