#### Cognitive functioning and emotional inhibition

##### PASAT

A non-adaptive version of the PASAT will be included as a measure of task-specific transfer of the CCT [24]. Comparable to the aPASAT, participants are presented with a continuous auditory stream of numbers of which they have to add the two last-heard digits. The task is presented in three trial blocks with ISIs of 3000, 2000, and 1500 ms, respectively. The task will be completed at T0 and T1.

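### The mediation step names a tool that does not match the plan's own ITT and nesting commitments, and leaves open a same-visit model that cannot test the hypothesised order

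*Protocol article*

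**What the plan says.** The third aim in the protocol article (Aims and hypotheses) is about order in time: "hypothesizing that improvements in depressive symptoms will follow improvement of working memory and reduction of rumination in the intervention group".

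The analysis is set in Evaluation of clinical outcomes: "Rumination and working-memory functioning will be evaluated as potential mediators of change in depressive symptoms", "for which Hayes’ PROCESS macro (in SPSS) will be used". No outcome time point, lag, covariate set, clustering or missing-data method is given for this step. The same section opens with a general rule: "All analyses will be conducted in agreement with the intention-to-treat (ITT) principle as per the CONSORT statement". For the clinical outcomes it specifies a mixed model with assessments within participants and participants within clinicians. Sample size calculation adds no allowance for loss to follow-up, on the ground that mixed models or multiple imputation will be used.

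The measurement schedule is fixed in Table 1 and the Measures text:
- The RRS "will be used to assess trait rumination [46] at T0 and T1".
- The BFT is "also administered at T0 and T1 only, serves to measure state rumination".
- For the PASAT: "The task will be completed at T0 and T1". The RNG has the same schedule.
- The IDS-SR is taken at T0, T1, T2, T3 and T4.

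Table 1 gives the PASAT and the RNG the same target concept, working memory capacity. The PASAT section describes the first differently: "A non-adaptive version of the PASAT will be included as a measure of task-specific transfer of the CCT".

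**The concern.** Three things do not fit together.

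First, the named tool. In standard form the PROCESS macro fits ordinary single-level regressions and deletes any row with a missing value. That is a property of the software and is not stated in the article. Used that way, it would depart from the ITT rule, the clinician nesting and the stated handling of missing data, and the text does not say how these are to be reconciled.

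Second, timing. Each mediator has one post-baseline value, taken at the same assessment as the T1 IDS-SR. Regressing T1 symptoms on a T1 mediator satisfies the wording, but it cannot separate a mediator that moves mood from mood that moves the mediator.

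Third, the working-memory mediator is not tied to a measure. The PASAT is a fixed-pace form of the training task, so a gain in the CCT arm may be practice.

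At stake is the mechanism claim of the third aim: it could report mediation that is reverse causation or task practice.

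**Working it through.** **Inputs from the article:** d = 0.45, power 0.80, two-sided α = 0.05, r = 0.50, mean cluster size 10, cv 0.475, icc 0.05, design effect 1.56, n = 33 then 52 per arm, 104 in total (Sample size calculation). No figure is given for mediation.

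**1. The plan's own figures.** With three follow-ups and equal correlations, n = 2(1.960 + 0.842)²/0.45² × [(1 + 2×0.5)/3 − 0.5²] = 77.5 × 0.4167 = 32.3, so 33 per arm. Design effect = 1 + [(1 + 0.475²)×10 − 1]×0.05 = 1.563. Then 33 × 1.56 = 51.5, so 52 per arm and 104 in total. These reproduce.

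**2. Same-visit model when mood drives the mediator.** Let T1 symptoms be Y = 0.45X + e with var(e) = 1, and let M = rY + noise with variance 1 − r². M has no effect on Y. A same-visit model finds a = 0.45r and b = r, so ab = 0.45r², a share r² of the total effect. The value of r is an assumption:
- r = 0.3: ab = 0.041, 9%
- r = 0.5: ab = 0.225 × 0.5 = 0.1125, 25%
- r = 0.7: ab = 0.221, 49%

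The true mediated share is zero each time.

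**3. What the schedule can support.** This was simulated with 3,000 runs per case, single-level, without missing data, declaring mediation when both paths are significant. Adjusted means that T1 IDS-SR enters both equations. All path coefficients are assumed:
- Reverse causation: Y1 = 0.5Y0 − 0.45X; M1 = 0.5M0 + 0.4Y1; Y2 = 0.5Y1 + 0.2Y0; plus noise.
- True lagged mediation: M1 = 0.5M0 − 0.6X; Y2 = 0.4Y1 + 0.4M1; plus noise, with no treatment effect on Y1.

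| Truth | n | T1 mediator, T1 outcome | T1 mediator, later outcome | Same, adjusted for T1 IDS-SR |
|---|---|---|---|---|
| Reverse causation | 104 | 18.1% | 9.3% | 0.07% |
| Reverse causation | 84 | 15.6% | 6.8% | 0.27% |
| True lagged mediation | 104 | 4.8% | 93.3% | 94.7% |
| True lagged mediation | 84 | 5.4% | 83.5% | 86.9% |

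Under these assumptions the same-visit model declares mediation that is absent and misses mediation that is present. The lagged model can be fitted with the scheduled data.

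**4. What the adjustment costs.** Suppose M improves mood before T1 and later symptoms depend on M only through T1 symptoms. Then, given T1 IDS-SR, M is unrelated to T2 IDS-SR, so b = 0 and real mediation is missed. The second scenario above has no effect before T1 and so favours the adjusted model.

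**5. Ignoring the clinician level.** If the full design effect applied, standard errors would be too small by a factor of √1.56 = 1.25. This is an upper bound. For the path from mediator to outcome, the inflation depends on the product of the two intraclass correlations. If the mediator's were also 0.05 (assumed), it is 1 + 11.256 × 0.05 × 0.05 = 1.028, a factor of 1.01.

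**6. Listwise deletion.** With an assumed 10%, 20% or 30% incomplete, 94, 83 or 73 of 104 remain. Standard errors widen by √(104/94) = 1.05, √(104/83) = 1.12 or √(104/73) = 1.19, before any selection bias.

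**The case against.** The strongest reply is that the article never states a same-visit model. It names no outcome time point, IDS-SR runs to T4, and PROCESS itself can fit a T1 mediator with a T2 outcome on one row per participant. Lag and covariates for a third-aim analysis are often left to an analysis plan, which is not shown here. This stands against several stronger readings that a reader might infer:

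- That the temporal hypothesis is untestable in this trial. It is not: T2 to T4 permit a lagged test.
- That the mediators are measured only after training. They are measured at T0 and T1.
- That a complete-case analysis is planned. The article does not say so. Imputation before running the macro is possible, multiple imputation is one of its stated options, and Procedure asks participants who stop training to complete all later assessments.
- That the PASAT will be the mediator. The article does not say so. The RNG is an untrained alternative, Aims and hypotheses separates near from far transfer, and the point does not touch rumination.

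The reply also limits the clustering harm. Participants are allocated individually, so clinicians can have patients in both arms, and the factor of 1.25 is only a ceiling.

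It does not remove the point. The article does fix a tool and a schedule. The tool in standard form does not follow the article's own general rules, and the wording admits a model that cannot address its own hypothesis.

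**Conclusion.** The point holds in limited form. As written, the mediation step does not reconcile PROCESS with ITT, nesting and the stated missing-data approach. It also does not commit to the lagged model that the hypothesis needs.

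The timing matters most: a same-visit analysis would show 9% to 49% spurious mediation for assumed correlations of 0.3 to 0.7. Clustering and deletion are smaller: a factor between about 1.01 and 1.25 on standard errors for the first, and 1.05 to 1.19 for the second at 10% to 30% loss. These sizes rest on assumed correlations, path coefficients and loss rates, since the article gives none for mediation.

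Even a well-specified lagged model stays open to mediator–outcome confounding. It also cannot show the order of changes before T1, nor cross-lagged effects after T1, because the mediators are not repeated. The change is worth making, but it concerns a third aim.

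**What to change.** Before results are seen, state:

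1. Mediator: the T1 value, adjusted for its T0 value. Outcome: IDS-SR at T2, adjusted for T0 IDS-SR, with T3 and T4 as supportive.
2. Results with and without adjustment for T1 IDS-SR, naming the equations it enters. The adjustment guards against reverse causation but removes mediation already complete by T1, so neither version suffices alone.
3. Fitting on multiply imputed data or by full-information likelihood, with clinician clustering and bootstrap intervals. Stata is already listed and can do this.
4. RNG as the main working-memory mediator, with the PASAT reported separately as a task-specific, near-transfer measure. This choice is partly one of judgement; the essential step is to keep the two apart.

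The cost is revised wording and some programming, with no new data. The lagged indirect effect will be less precise than a same-visit one, and the confounding caveat should be reported with it.
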